### Assessments

For patient outcome we will collect data concerning the LOS, admission to and duration of ICU stay, readmission within 30 days and mortality in hospital or within 30 days after discharge for the baseline group and the intervention group. Furthermore we will collect data for possible confounders of patient’s outcome, namely age, sex, community-or hospital acquired infection, Charlson comorbidity index [15,16], use of antibiotics during the previous 30 days, and clinical condition as assessed by the Modified Early Warning System [17]. To calculate QI performance we will collect data concerning the number of taken blood cultures including its results, the number of taken cultures of suspected sides of infection including its results, antibiotic use including dose, interval and duration of treatment in days, the (suspected) type of infection and relevant laboratory parameters. For the spill over group, we will only collect data concerning the LOS and the possible confounders.

Antibiotics included in the study belong to group J01 (antimicrobials for systemic use) of the Anatomic Therapeutic Chemical (ATC) classification system. When multiple antibiotics are prescribed to one patient, all antibiotics will be registered. Antiviral therapy, medication for tuberculosis, antibiotics used for non-systemic selective intestinal decontamination and antibiotics used as pro-kinetics will be excluded.

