**The stepped wedge design for checklist implementation.**

To promote selection of a patient population representative for every day clinical practice in the Netherlands, two university hospitals and seven teaching hospitals will participate, and in each hospital at least one surgical and one non-surgical ward will be included. The ICU and the paediatric ward will be excluded, as the quality indicators do not apply to these populations. Patients with a suspected bacterial infection presenting on the emergency department (ED) will be included if they are going to be hospitalized on one of the participating wards.

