### Sample size

The power analysis is based on previous results of appropriate antibiotic use on length of stay as described at ‘background’ [6,7]. In a simulation study based on the stepped wedge design, with nine hospitals each contributing 180 patients with a suspected infection, we estimated the power to approximate 80% to demonstrate a significant reduction of 13% in length of stay, assuming that the intraclass correlation coefficient does not exceed 0.20. With each hospital contributing 180 patients with a suspected infection, the total sample size will be 1620 patients. For each hospital we have determined a minimum number of patients in the baseline group and intervention group, depending on the randomization order of the hospital in the stepped wedge.

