### Analysis

#### Effect evaluation

We will use mixed linear models to analyse the overall effect of the introduction of the checklist on length of stay. Therefore we will evaluate differences between baseline (before introduction of the checklist) and intervention plus spill over (after introduction of the checklist) (intention to treat analysis). We will also determine the theoretical effect of the checklist on LOS by evaluating differences between baseline and intervention data without the spill over data (per protocol analysis). Differences between the baseline data and the intervention data for secondary outcomes will also be evaluated with mixed linear models. For dichotomous outcomes (mortality), the comparison will be evaluated with a similar approach, using generalized estimating equation models. These mixed models account for within-cluster dependencies, and allow adjustment for possible confounders. To assess whether differences between these groups may be explained by confounding patient characteristics, we will first test with multivariate multilevel (linear mixed) analyses if these variables have a significant effect (p < 0.05) on the outcomes. Hereafter, we will compute the estimate of the total causal effect of checklist implementation on the outcomes before and after adjusting for a significant variable. If the estimate varies 10% or more, possible confounding is present and in that case we will adjust for this variable.

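### The intention-to-treat analysis of length of stay cannot adjust for type of infection, which is not a listed confounder and is not collected in the spill over group; ward type is also unlisted

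*Protocol article*

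**What the plan says.** Assessments (protocol article) names six possible confounders of outcome: "namely age, sex, community-or hospital acquired infection, Charlson comorbidity index [15,16], use of antibiotics during the previous 30 days, and clinical condition", with clinical condition measured by the Modified Early Warning System. The next sentence turns to data for quality indicator performance, and only there does type of infection appear: "duration of treatment in days, the (suspected) type of infection and relevant laboratory parameters". The paragraph ends: "For the spill over group, we will only collect data concerning the LOS and the possible confounders".

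Effect evaluation sets two contrasts for LOS. The intention-to-treat contrast is between "baseline (before introduction of the checklist) and intervention plus spill over (after introduction of the checklist) (intention to treat analysis"). The other is described as "evaluating differences between baseline and intervention data without the spill over data (per protocol analysis"). A covariate is adjusted for only if it is significant at p < 0.05 and then moves the estimate by 10% or more.

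On wards, Study design and setting states that "in each hospital at least one surgical and one non-surgical ward will be included". On numbers, Sample size states: "For each hospital we have determined a minimum number of patients in the baseline group and intervention group". No split by ward is mentioned there.

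**The concern.** The trial pools all suspected bacterial infections, on surgical and non-surgical wards, into one LOS comparison. Site of infection and surgical care are likely to be prognostic for LOS, and the six listed covariates stand in for them only in part. Each hospital moves one way from control to intervention within eleven months. Its intervention patients are therefore always later than its control patients, and the study does not cover a full seasonal cycle. If the infection or ward mix of a hospital differs between its two periods, an unadjusted part of that difference can enter the estimated checklist effect on the primary endpoint.

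The gap for type of infection lies in data collection. A statistical analysis plan can add a model term, but it cannot adjust for a variable that was never recorded in part of one comparison group. The omission is also unnecessary, because the variable is already collected in the other two groups.

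**Working it through.** **1. Which analysis can use which variable.** Set side by side, Assessments and Effect evaluation give:

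| Variable | Baseline | Intervention | Spill over | Usable in ITT | Usable in per protocol |
|---|---|---|---|---|---|
| Six listed confounders | yes | yes | yes | yes | yes |
| Type of infection | yes | yes | no | **no** | yes, but not listed |
| Ward type | not listed, but known from eligibility | same | same | yes, if specified | yes, if specified |

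So the protocol's own confounder rule (p < 0.05, then a 10% change) cannot be run for type of infection on the intention-to-treat set. On the per protocol set it could be run, but as written it would not be, because the variable is not on the list.

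**2. The plan's own numbers.** 9 × 180 = 1620 = 2 × 810, as stated. The stated power of about 80% cannot be checked because no SD of LOS is given, but it does not bear on this point.

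**3. Scale of the target effect.** The target is a 13% reduction in LOS. The Background gives 7.3 and 8.7 days from a urinary tract infection study. These serve only as a scale.
- 0.13 × 7.3 = 0.95 day
- 0.13 × 8.7 = 1.13 days
- The 10% change threshold, if the estimate equals the target, is 0.095 to 0.113 day.

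**4. Illustrative bias.** Bias = (net change in the share of a patient group between periods) × (difference in mean LOS between that group and the rest). The documents give neither input, so both are assumed. The listed covariates, and any period term, are taken to carry none of the shift.

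| Shift in share | LOS gap | Bias | Share of target (1.13 to 0.95 day) |
|---|---|---|---|
| 5 points | 2 days | 0.05 × 2 = 0.10 day | 9% to 11% |
| 10 points | 2 days | 0.10 × 2 = 0.20 day | 18% to 21% |
| 10 points | 3 days | 0.10 × 3 = 0.30 day | 27% to 32% |

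The first row already lies at about the protocol's own threshold. To imitate the whole target with a 3-day gap, the share would have to move by 0.95/3 = 32 to 1.13/3 = 38 points.

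**5. What chance alone would do.** With 810 against 810 patients and clustering ignored, the standard error of a difference in a share p is √(2p(1−p)/810). This is 2.3 points at p = 0.3 and 2.5 points at p = 0.5. A net shift of 5 points is about two such standard errors, and 10 points about four. Clustering would raise the standard error, and the spill over patients added after introduction would lower it somewhat.

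**The case against.** A reader might infer that case-mix shifts will be taken for a checklist effect. The documents do not support that.
- The order of hospitals is randomized. Patients are identified from a pharmacy overview whether or not a checklist was completed, and the intention-to-treat set keeps all of them. No shift is built into the design.
- A shift shared by all hospitals would be absorbed by a period term. Effect evaluation names none, but an article may leave that to the analysis plan. Hospital-specific drift has no built-in direction, so it tends to add noise more than systematic bias.
- Acquisition setting, Charlson index, previous antibiotics and the early warning score carry part of the case mix. The figures above ignore this.
- A net shift of 10 points is larger than chance would readily produce, and the LOS gaps have no source in the documents.

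These points stand, and they make the problem a conditional risk.

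The ward part is also weaker than it looks. Ward participation is part of eligibility, so ward is known for every patient, spill over included. Effect evaluation leaves the cluster levels unnamed, so ward could enter there. Nor does the article's silence on ward quotas show that none exist. A reader might also infer that the per protocol comparison cannot be adjusted for type of infection. It can, since both of its groups have the variable. Selection by checklist completion in that comparison is a separate matter that these covariates would not cure.

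None of this answers the core point. Type of infection is absent from the spill over group, so the intention-to-treat analysis cannot use it.

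**Conclusion.** The point holds in a limited form. As written, the intention-to-treat analysis of the primary endpoint cannot adjust for type of infection, a likely prognostic variable that is already collected in the other two groups. Ward type is known for everyone but is not listed. If either mix differs between periods within hospitals, and the listed covariates do not carry the difference, part of it may be read as a checklist effect.

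The illustrated size runs from about a tenth of the target effect (5 points, 2 days) to about three tenths (10 points, 3 days). Every shift and gap is assumed, and the LOS scale is borrowed from urinary tract infections. The omission could distort the estimate but would not by itself plausibly produce the whole target effect. Acting is justified because the remedy is cheap and the gap is hard to repair once data collection is over.

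**What to change.** In Assessments, add two items to the confounder list: suspected type of infection at the start of antibiotics, in a few broad groups, and ward type (surgical or non-surgical). Record type of infection for spill over patients as well.

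In Effect evaluation, state that both enter the LOS models, intention-to-treat and per protocol, as prespecified fixed effects. State also that they are exempt from the p < 0.05 and 10% change-in-estimate selection. Without that exemption, adding them to the list would only submit them to the selection rule, and the text would contradict itself. For sparse dichotomous outcomes such as mortality, use fewer infection categories, because events rather than patients limit what the model can carry.

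The cost is one more chart item per spill over patient, for whom six confounders are already collected, and a few model degrees of freedom. Ward type needs no new chart review. No sample size figure changes.

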### Phase 2: cluster randomized clinical trial to evaluate the AB-checklist

#### Study design and setting

The (cost-) effectiveness of introducing the antibiotic checklist will be studied in a controlled, multicentre, prospective study using a stepped wedge design, comparing outcomes before and after implementation of the checklist while accounting for potential confounders [14].

The checklist will be introduced in nine hospitals over four time periods, during a total study period of eleven months (Figure 2). The aim is to include at least 810 patients in the period before- (the baseline group), and at least 810 patients with a completed checklist in the period after checklist introduction (intervention group). During the transition period implementation activities will be started and no patients will be included. This period runs from one month before introduction of the checklist to one week after introduction. Since compliance to the checklist will not be 100%, we will also collect data concerning the LOS from the patients in whom the checklist should have been but was not completed during the period after checklist introduction (the spill over group).

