### Patient enrolment

#### Eligible patients

The physician will use the checklist in all hospitalized adults (≥18 years old), or adults at the ED who will be admitted at a participating ward, with a suspected community-acquired and/or hospital-acquired bacterial infection, and will be treated with intravenous antibiotics. The treating physician identifies these patients upon prescription of antibiotic therapy. The patients included in the study are all patients that meet the above mentioned inclusion criteria, whether they have a completed checklist or not (see Figure 3 for the flowchart). They will be included in each hospital using an overview of the patients who started with intravenous antibiotics. This overview will be generated by the local departments of hospital pharmacy from the computerized physician order entry systems. Patients are excluded from the study in case of anticipated hospital stay of less than 24 hours, antibiotics used as prophylaxis or intended for less than 24 hours, hospitalization at the ICU at the start of the treatment, transfer from another hospital, or antibiotic treatment in the ambulance before presentation at the ED.

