#### Economic evaluation

The key question for the economic evaluation is whether the benefits of using the checklist, which will likely include reduced antibiotic use, reduced length of stay and associated costs, justify the costs associated with implementation activities as well as daily use of the checklist. For reasons of feasibility, the cost analysis will only include a few main cost drivers of health care utilization, namely LOS on a general or ICU ward and antibiotic use. Unit costs for health care utilization will be estimated according to the Dutch guideline on (unit) costing in health care [18]. LOS and ICU stay will be valued based on the guideline prices. Furthermore, we will compare the total antibiotic use in days per antibiotic class in the baseline and the intervention group. Antibiotic costs will not be valued because the benefits become more evident in terms of reduced quantities rather than their particular costs. Implementation costs will be divided in non-recurring and recurring costs. Non-recurring costs are related to our study, such as costs of the development of the materials, the implementation strategy and costs of evaluation of the implementation. Recurring costs are the costs of accomplishment of the implementation strategy. The primary analysis is a cost-effectiveness analysis, with the incremental cost-effectiveness ratio expressed as the implementation related costs per reduction of length of stay in days. As we hypothesize that an effective implementation of the checklist will result in reduced health care use and thus lower costs, we will also perform a cost-benefit analysis, evaluating whether the implementation costs are offset by this cost reduction (costs of implementation < health care cost reduction). Robustness of the results for uncertainty in the assumptions will be evaluated in sensitivity analyses, including estimates of unit costs and volume of implementation activities (considering less activities will be needed if checklists become part of standard care). In a budget impact analysis results from the economic evaluation will be extrapolated to the national level to estimate the total clinical and budget impact in terms of health benefits, reduction in antibiotic use, and associated economic impact on the health care budget per annum for the Netherlands. The budget impact analysis will be performed according to the criteria provided by Mauskopf et al. [19], from a societal perspective as well as from the health insurance and/or national health care budgeting framework perspective. We will evaluate the impact of varying implementation rates, comparing care as usual (0% implementation), potential impact (100% implementation), and the probable rates of 85% and 50% implementation.

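### Secondary clinical, antibiotic-use and quality endpoints are not collected for post-introduction patients without a completed checklist, so they can only be compared per protocol, not as the effect of introducing the checklist

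*Protocol article*

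**What the plan says.** Under Study design and setting, the protocol article splits eligible post-introduction patients in two. The recruitment target is "at least 810 patients with a completed checklist in the period after checklist introduction (intervention group"). LOS data are also to be gathered from "the patients in whom the checklist should have been but was not completed during the period after checklist introduction (the spill over group"). Eligible patients counts both groups as included, "whether they have a completed checklist or not".

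Assessments then treats the groups differently. The list of outcome data (LOS, ICU admission and duration, readmission) ends with "mortality in hospital or within 30 days after discharge for the baseline group and the intervention group". The culture, antibiotic and laboratory data needed to score the QIs come next. The paragraph closes with: "For the spill over group, we will only collect data concerning the LOS and the possible confounders".

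Effect evaluation follows the same split. For LOS, baseline is compared with "intervention plus spill over (after introduction of the checklist) (intention to treat analysis"), and a second comparison without the spill over patients is called per protocol. For the other endpoints the plan is: "Differences between the baseline data and the intervention data for secondary outcomes will also be evaluated with mixed linear models". Dichotomous outcomes get a similar approach with generalized estimating equations, and no wider group is named. Economic evaluation compares antibiotic days between the baseline and intervention groups, and gives the health care cost drivers as "namely LOS on a general or ICU ward and antibiotic use".

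The Objectives state the aim as the effect of introducing the checklist on ICU and hospital stay, adequate treatment, mortality, antibiotic use and costs.

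**The concern.** Hospitals are randomised to the time of introduction. Whether a checklist is completed for a given patient is not randomised. It is decided afterwards by the treating physician and has no equivalent in the baseline period. A comparison of all baseline patients with completers alone therefore mixes any effect of the checklist with any difference between patients who do and do not get one. For LOS the plan recognises this: it sets an intention-to-treat contrast and describes the completers-only result as a theoretical effect. The secondary endpoints get the completers-only contrast without that label and without the alternative.

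This is a limit on data collection, so an analysis plan cannot repair it later. At stake is whether a reported difference in mortality, ICU use, readmission or antibiotic use can be read as an effect of introduction. A change in these outcomes among patients without a checklist would also go unseen.

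**Working it through.** **1. The plan's own figure.** Sample size gives 9 hospitals × 180 = 1620 patients, which equals 810 baseline + 810 with a completed checklist. The arithmetic reproduces. Spill over patients come on top of the 810 completers. The power statement concerns LOS only and plays no part here.

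**2. What is available after introduction** (from Assessments, Effect evaluation and Economic evaluation):

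| Endpoint | Completers | Spill over | Intention-to-treat contrast possible? |
|---|---|---|---|
| LOS | yes | yes | yes, and planned |
| ICU admission and days | yes | no | no |
| Readmission within 30 days | yes | no | no |
| Mortality, in hospital and to 30 days after discharge | yes | no | no |
| Total antibiotic use | yes | no | no |
| QI performance | yes | no | no |
| Implementation cost per LOS day reduced | – | LOS available | yes |
| Hospital-stay cost priced by ward type | yes | total LOS only | not with ICU days priced separately |

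**3. Number without secondary outcomes.** If a proportion c of eligible patients has a completed checklist, 810 completers imply 810/c eligible patients and 810/c − 810 with no secondary outcomes. The article says only that compliance will fall short of 100%, so c is assumed. I take 0.85 and 0.50 as an illustrative range. The same two values appear in the budget impact analysis, but as national implementation scenarios, not as forecasts of trial compliance.

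- c = 0.85: 810/0.85 ≈ 953 eligible, so about 143 (15%) have none.
- c = 0.50: 810/0.50 = 1620 eligible, so 810 (50%) have none.

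**4. Size of the distortion when the checklist does nothing.** Let p be the overall risk, the same before and after introduction, p₁ the risk in completers and r·p₁ the risk in non-completers. Then p = c·p₁ + (1−c)·r·p₁, so the apparent risk ratio of completers to baseline is

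p₁/p = 1/(c + (1−c)r).

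| c (assumed) | r = 0.5 | r = 1.5 | r = 2 |
|---|---|---|---|
| 0.85 | 1/0.925 = 1.08 | 1/1.075 = 0.93 | 1/1.15 = 0.87 |
| 0.50 | 1/0.75 = 1.33 | 1/1.25 = 0.80 | 1/1.5 = 0.67 |

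With r above 1, selection imitates a benefit. With r below 1, it hides a benefit or imitates harm. The documents do not say which applies. These are crude ratios, before covariate adjustment.

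**The case against.** The strongest reply is that the primary endpoint is untouched. LOS is collected for every eligible patient and has an intention-to-treat analysis, and the sample size rests on LOS alone. That stands, and it confines the point to secondary endpoints.

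A second reply is that confounders are collected in all groups, including age, sex, infection origin, Charlson index, prior antibiotics and the early warning score, and that adjustment is planned. Completers and non-completers can also be compared on severity and on LOS. This helps, but only in part. Effect evaluation adjusts only for variables that are significant at 0.05 and shift the estimate by 10% or more. Ward workload and the prescriber are not on the list. No adjustment supplies outcomes that were never extracted.

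Three stronger readings are tempting, and the documents do not support them.

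- *A reader might infer that the whole economic evaluation fails.* The primary ratio is implementation cost per LOS day reduced, and LOS exists for all patients. Antibiotic costs are expressly not valued, so missing antibiotic days cannot bias net cost. Two narrower problems remain: spill over LOS cannot be divided into ICU and ward days for pricing, and an antibiotic-use reduction seen in completers would be carried into the national budget impact analysis.
- *A reader might infer that selection must flatter the checklist because non-completers are sicker.* Nothing in the article says why checklists are left incomplete. Physicians might complete them more often for sicker patients. If completion requires the second bundle, due by 72 hours at the latest, early death or discharge could also decide who counts as a completer, but the article does not define this.
- *A reader might turn the risk ratios into a false-positive rate for mortality.* That needs a mortality rate and an allowance for clustering, and the article gives no mortality rate.

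**Conclusion.** The point holds in this limited form. For mortality, ICU admission and duration, readmission, total antibiotic use and QI performance, the plan can deliver only a per-protocol contrast formed after randomisation, although the Objectives state these as effects of introducing the checklist. No other section of the article repairs this.

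The size is uncertain because completion and the non-completer risk are both unknown. Over the assumed range, with no true effect, the apparent risk ratio runs from 0.87 to 1.08 at 85% completion and from 0.67 to 1.33 at 50% completion. This also assumes that the underlying risk of eligible patients does not change between the periods. The primary LOS analysis and the primary cost-effectiveness ratio are not affected.

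**What to change.** Extend extraction in the spill over group to ICU admission and days and in-hospital mortality and, where records allow, to 30-day mortality, 30-day readmission and antibiotic days. For these endpoints, and for pricing ICU and ward days, make baseline versus all post-introduction patients the main contrast and keep the completers-only comparison as supportive. Label any endpoint that is not extended, such as the QI scores, as per-protocol, and do not report it as the effect of introduction. In the budget impact analysis, state which population any antibiotic-use reduction comes from.

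The cost is modest. Spill over patients are already listed from the hospital pharmacy overview, counted for the compliance calculation, and extracted for LOS, Charlson index and early warning score. No new patients are needed. The real extra work is record extraction, chiefly for the 30-day outcomes and treatment duration, because the article does not show that the LOS record or the pharmacy overview supplies them. The change should be made while extraction is still open, since outcomes not collected then may be hard to recover.
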